### Objectives

1.2

1.Research hypothesis: 3-row staplers are noninferior to 2-row staplers in colorectal anastomosis formation with respect to anastomotic leakage rate, meaning that AL rate in 3-row-stapled colorectal anastomoses is at least not higher than that of 2-row-stapled anastomoses within 5% noninferiority margin.2.Study objectives2.1.Primary objective: to determine if 3-row staplers are noninferior to 2-row staplers (noninferiority margin Δ = 5%) in the endpoint of anastomotic leakage rate determined by X-ray or computed tomography (CT) scan in subjects undergoing LAR for rectal cancer.2.2.Secondary objectives2.2.1.Key secondary objectives2.2.1.1.Evaluate the incidence of anastomosis-related complications, including anastomotic bleeding and para-anastomotic abscess formation2.2.1.2.Determine the impact of the stapler type on overall and cancer-related quality of life using short form (36) (SF-36) and quality-of-life questionnaire core 30 (QLQ-C30) questionnaires, respectively2.2.2.Other secondary objectives2.2.2.1.Assess the incidence of LAR syndrome (LARS) and level of incontinence during postoperative period in patients with stapled colorectal anastomosis.2.2.2.2.Determine the impact of the stapler type on incontinence, assessed with the Cleveland clinic incontinence score (CCIS) questionnaire.

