#### Late postoperative period

2.3.5

It is defined as the time period starting at 31st day postsurgery. At weeks 4 to 6, according to the standard protocol, the preventive stoma is closed. Also, the patient is asked to fill out the questionnaire forms SF-36, QLQ-C30, LARS, and CCIS to assess the changes in the quality of life of the patient relative to the baseline level.

Following discharge, all subjects will be required to provide 4 filled out questionnaires (SF-36, QLQ-C30, CCIS, LARS), and report their pain level using the VAS. To ensure patient compliance to protocol requirements, all subjects will be notified telephonically and/or via e-mail. If the patient is unavailable, he or she must be contacted at least 3 times within the follow-up timeframe, before considered dropped-out from the study.

All subjects are strongly advised to adhere to bland diet, and are recommended to abstain from the intake of meat and fatty meals within at least 1 month after stoma reversal. Patients are also advised to minimize the intake of NSAIDs in the absence of comorbidities requiring NSAID treatment. NOAC administration is necessary during the 1st week after surgery to minimize the risk of thrombosis.

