#### Primary outcome measure

2.4.1

The primary outcome measure is the difference between the 2 groups in the incidence of colorectal anastomosis leakage documented with an X-ray and/or CT scan in the time period between the LAR and stoma reversal surgery.

As proposed by the International Study Group of Rectal Cancer, AL is defined as a “defect of the intestinal wall integrity at the colorectal or coloanal anastomotic site (including suture and staple lines of neorectal reservoirs) leading to a communication between the intra- and extraluminal compartments,” or presence of “a pelvic abscess close to the anastomosis.”^[14]^ In context of primary outcome analysis only presence or absence of diagnosed AL (dichotomous aggregation method) from the day of intervention to preventive stoma reversal will be considered. The timeframe for the primary outcome measure is defined as the period between the initial surgery and stoma reversal, which usually takes place at 4 to 6 weeks after LAR, and may differ significantly between subjects due to variability of AL presentation and symptoms. Additionally, AL may be asymptomatic and discoverable only with imaging studies, which are only necessary to ensure the safety of stoma reversal surgery.

All patients undergoing LAR with stapled colorectal anastomosis formation will be treated according to intervention protocol described in the corresponding section. The patients’ status will be monitored twice a day during rounds. AL has a multifaceted clinical course and has no pathognomonic features; it may be asymptomatic and require no intervention, or it can lead to serious complications, such as peritonitis and sepsis. The clinical signs of AL include the following:

1.General1.1. Fever (≥38.0°C)1.2. Tachycardia (≥100/min)1.3. Increased respiratory rate (≥30/min)1.4. Renal insufficiency (<30 mL/h or <700 mL/d)1.5. Altered mental status (agitation/lethargy, GCS < 15)1.6. Deterioration of overall clinical condition1.7. Peritonitis (clinical signs of abdominal guarding, rebound tenderness, abdominal pain worsening with movement, etc)1.8. Sepsis (qSOFA ≥ 2)2.Local2.1. Bowel obstruction2.2. Abnormal drain content (purulent/turbid/air)2.3. Purulent or fecal vaginal discharge (rectovaginal fistula)2.4. Abdominal pain other than wound pain2.5. Fascial dehiscence3.Laboratory signs include:3.1. Leukocytosis3.2. C-reactive protein elevation

There are several ways in which AL can be diagnosed in the investigated subjects (Fig. 1).

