1.If any of these clinical signs prompting the attending surgeon to suspect AL are present, the patient will undergo imaging studies for further evaluation. If there is no evidence of nonanastomotic complications, an X-ray with contrast enema will be performed. In presence of any clinical signs of nonanastomotic complications (pancreatitis, pneumonia, etc), a CT scan of the chest, abdomen, and pelvis with contrast enema will be obtained to simultaneously exclude anastomosis-unrelated postoperative complications. If CT results suggest AL, the patient will reach the primary endpoint, and will be treated accordingly to their condition. Further treatment will not be discussed in this protocol as it is irrelevant to endpoint analysis.2.If there are no symptoms suggesting AL before discharge, the subject will undergo X-ray with contrast enema as a part of preoperative assessment prior to stoma reversal procedure in 4 to 6 weeks after the initial surgery according to the standard protocol implemented at the study center. If the X-ray findings suggest AL, the subject will reach the primary endpoint.

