## Discussion

3

This is the 1st prospective randomized clinical trial comparing the efficacy and safety of 2- and 3-row-stapling techniques in LAR for rectal cancer. This study will primarily focus on short-term outcome assessment that will allow to gather preliminary information about the use of 3-row circular staplers in rectal cancer surgery.

The design of this study has certain limitations. Firstly, there is no definitive way to exclude all the preoperative and intraoperative risk factors of AL due to their large number and the presence of nonmodifiable risk factors, such as male gender, the need for preoperative chemo-/radio-/chemoradiotherapy, or tumor size. Moreover, broadening of exclusion criteria with regard to modifiable risk factors, such as tobacco use would hinder patient recruitment significantly, and thus would delay the acquisition of definite conclusions. Additionally, whether open or minimally invasive, TME ends with rectum transection below the inferior tumor margin using a linear cutter stapler followed by colorectal anastomosis formation with a circular stapler. Thus, the quality of both linear mechanical suture on the rectal stump and of the circular stapled anastomosis between the proximal colon and the distal rectal stump influence the integrity and healing rate of colorectal anastomosis. However, in the context of this study the distance of anastomosis from the anal verge is limited to LARs, which will help to achieve homogeneity of the study groups.

Another issue is the uncertainty of the definition of AL. In this protocol, we have referred to the definition of AL proposed by the International Study Group of Rectal Cancer describing it as a “communication between the intra- and extraluminal compartments owing to a defect of the integrity of the intestinal wall at that anastomosis between the colon and rectum or the colon and anus.”^[14]^ Because there are numerous definitions of AL, diagnostic approaches vary greatly between different studies. However, the algorithm of AL diagnosis outlined in this paper allows to detect both clinically significant and asymptomatic forms of AL ensuring adequate primary outcome assessment.

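### The primary leak endpoint runs to stoma reversal, a date that varies with the leak's own presentation, and counts imaging evidence only, so unreversed stomas and leaks first proven at reoperation have no workable rule

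*Protocol article*

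**What the plan says.** Section 2.4.1 (Primary outcome measure) sets the window: "The timeframe for the primary outcome measure is defined as the period between the initial surgery and stoma reversal". It says reversal usually falls 4 to 6 weeks after resection, but that the period "may differ significantly between subjects due to variability of AL presentation and symptoms". The outcome is binary: "only presence or absence of diagnosed AL (dichotomous aggregation method) from the day of intervention to preventive stoma reversal will be considered". Section 2.3.5 (Late postoperative period) is categorical about timing: "At weeks 4 to 6, according to the standard protocol, the preventive stoma is closed".

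The Objectives and section 2.4.1 both require the leak to be shown by X-ray or CT. Section 2.4.1 then gives two diagnostic routes.

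- **Symptomatic route.** Signs that make the surgeon suspect a leak lead to imaging. This is a contrast X-ray when nothing points to a nonanastomotic complication, and CT otherwise. The sentence that closes this route is "If CT results suggest AL, the patient will reach the primary endpoint".
- **Routine route.** "If there are no symptoms suggesting AL before discharge, the subject will undergo X-ray with contrast enema", as part of the work-up before reversal.

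The definition in section 2.4.1 counts a pelvic abscess next to the anastomosis as a leak. The Objectives list, as a key secondary item, anastomosis-related complications "including anastomotic bleeding and para-anastomotic abscess formation". Among the secondary outcome measures, a grade C leak is one that needs relaparotomy, and reintervention for leak has a fixed 6-week frame.

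**The concern.** A binary endpoint is comparable across patients when everyone is observed to the same point with the same means of detection. Here the end of observation is a clinical event whose date, on the protocol's own account, moves with the outcome under study. The one test that finds silent leaks in routine patients is attached to the same event. Patients whose stoma is closed late have more time for a leak to be found. Patients whose stoma is never closed have no defined end and no scheduled look.

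The imaging-only rule is a second gap. A patient taken to relaparotomy without prior imaging, and found to have a leak, would be a non-event on the primary endpoint while meeting the grade C description and counting as a reintervention for leak.

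This matters more here than in a superiority trial. If the 3-row stapler is truly worse, missing leaks equally in both arms shrinks the observed difference and makes noninferiority easier to declare. Randomisation and blinding do not prevent that.

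**Working it through.** **1. The plan's own figure.** Inputs from section 2.6 (Sample size): one-sided alpha 0.05 (z = 1.645), power 80% (z = 0.842), margin 5 points, advantage of 12 points for the 3-row arm, leak rates 30% and 18%. With unpooled variance,

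n per arm = (1.645 + 0.842)² × [0.30 × 0.70 + 0.18 × 0.82] / (0.05 + 0.12)² = 6.18 × 0.3576 / 0.0289 = 76.5, rounded up to 77, or 154 in total (power 80.2%).

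The figure reproduces with 30% in the 2-row arm and 18% in the 3-row arm. The section's text attaches the 30% to the 3-row device; that is a separate matter. The calculation shows no allowance for undetected leaks.

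**2. The rules applied patient by patient.**

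| Patient | What the text gives |
|---|---|
| Leak diagnosed, reversal then delayed | Already an event; the delay adds nothing |
| No symptoms, reversed at 4-6 weeks | X-ray before reversal; clear |
| No diagnosed leak, reversed late | Longer window, X-ray at a later date |
| Stoma never reversed | No end of window, no scheduled X-ray |
| Leak first confirmed at relaparotomy, no imaging | Not a primary event, but fits grade C |
| Symptoms, positive X-ray, no CT | An event under the definition; not named in the symptomatic route |
| Symptoms, negative first imaging | Not named in the routine route |
| Pelvic abscess next to the anastomosis | A leak in 2.4.1, a separate secondary item in the Objectives |

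**3. What under-detection would do (illustration).** The documents give no detection rate, so these rates are assumptions. Put the truth at the margin: leak 18% in the 2-row arm (the centre's average in section 2.6), 23% in the 3-row arm, 77 per arm. Let s₂ and s₃ be the proportions of leaks detected. Then

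P(noninferiority) = Φ{ [0.05 − (0.23 s₃ − 0.18 s₂)] / SE − 1.645 }, SE² = [0.18 s₂(1 − 0.18 s₂) + 0.23 s₃(1 − 0.23 s₃)] / 77.

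For s₂ = s₃ = 0.80, the detected rates are 14.4% and 18.4%, the difference is 4.0 points, SE = √(0.2734 / 77) = 0.0596, and Φ(0.01 / 0.0596 − 1.645) = Φ(−1.477) = 7.0%.

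| Detection, 2-row / 3-row | Observed difference (points) | False noninferiority |
|---|---|---|
| 100% / 100% | 5.0 | 5.0% |
| 95% / 95% | 4.75 | 5.4% |
| 90% / 90% | 4.5 | 5.9% |
| 80% / 80% | 4.0 | 7.0% |
| 70% / 70% | 3.5 | 8.4% |
| 100% / 95% | 3.85 | 7.1% |
| 100% / 90% | 2.7 | 10.0% |
| 100% / 80% | 0.4 | 18.3% |

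The direction depends on the truth. If the 3-row arm really is 12 points better, 80% detection in both arms lowers power from 80.2% to 74.9%.

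**4. How many leaks could be involved.** Assume 5-20% of patients are not reversed (no figure is given). That is 0.05 × 77 = 3.9 to 0.20 × 77 = 15.4 per arm. At an 18% leak rate they carry 3.9 × 0.18 = 0.7 to 15.4 × 0.18 = 2.8 leaks per arm. If all were missed, detection would fall to 95-80%, which matches the equal-detection rows at 5.4% to 7.0%. Symptomatic leaks among them would still be imaged, which lowers the loss. A leak rate above 18% in unreversed patients would raise it.

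**The case against.** The best case against is that this is loose wording in a condensed article, and much of it stands.

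- A reader might infer that patients with leaks collect more events because their reversal is delayed. The binary endpoint rules that out: a diagnosed leak is counted once.
- A reader might infer that a positive X-ray does not count on the symptomatic route, or that a symptomatic patient with negative imaging gets no second look. The definition accepts X-ray or CT, the CT sentence directly follows the CT branch, and the routine X-ray is described as part of the work-up before reversal under the centre's standard practice. Figure 1, to which the text refers for these pathways, is not shown and may settle both. What remains is wording to reconcile.
- A reader might see two rival leak definitions, because the Discussion describes only a "communication between the intra- and extraluminal compartments owing to a defect of the integrity of the intestinal wall" and omits the abscess. It cites the same source as section 2.4.1 and is best read as an abbreviated restatement. Reporting abscess separately does not by itself exclude it from the leak count.
- The stated pathway sends suspected leaks to imaging, so a leak first found at relaparotomy implies a departure from it. That makes the case less common. It does not tell the analyst how to code it.
- Some unreversed patients fall under the postoperative exclusions (early death unrelated to leak, inability to complete procedures). How that fits the intention-to-treat analysis is a separate question, and a stoma simply left in place is still not covered.

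**Conclusion.** The point holds in a limited form. The window for the only primary endpoint ends at an event whose date varies with the outcome, and the systematic test is tied to that event. The harm is confined to suspected, missed or late leaks and to stomas not reversed. The imaging-only rule can also leave out a leak proven at relaparotomy. The X-ray and abscess wording needs reconciling, no more.

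The size cannot be derived from the documents. Under the assumed 95-80% detection in both arms, with leak rates of 18% and 23%, false noninferiority is 5.4-7.0% against a nominal 5.0%. The larger figures, up to 18.3%, need detection to fall in the 3-row arm alone, and nothing in the documents shows that. Random allocation and a blinded assessor limit it.

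A reader might also infer a bias as large as the margin because 4 of 77 patients is 5.2 points. That is true of any binary endpoint at this sample size and says nothing about how many patients would be misclassified here.

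**What to change.** 1. Define the primary event as a leak, including a pelvic abscess next to the anastomosis, shown on X-ray or CT or confirmed at endoscopy or reoperation. Count it from resection to one fixed calendar cut-off just after the planned 4-6-week interval, in all randomised patients whatever the stoma status.
2. State in section 2.4.1 that a positive X-ray on the symptomatic route reaches the endpoint, and that the routine X-ray before reversal applies to every patient without a prior leak, including those with earlier negative imaging.
3. Report abscess as a subset of leak, and align the Objectives with this.
4. For patients without imaging by the cut-off, use all available evidence and add a sensitivity analysis for undetected leaks. Do not require additional X-rays.
5. Keep the count to reversal as a sensitivity analysis.
6. Reconcile sections 2.3.5 and 2.4.1 on when reversal takes place. The timing itself is a clinical matter and is not proposed here.

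The cost is wording plus one sensitivity analysis for undetected leaks; the count to reversal is already planned. The downside is that leaks found only at a delayed reversal leave the primary count. Losing events can itself ease a noninferiority claim, so the analysis to reversal should be reported beside the primary one.

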**Figure 1 F1:**
[figure not shown]
Primary outcome measure. AL *=* anastomotic leakage, CT *=* computed tomography.

#### Secondary outcome measures

2.4.2

1.Severity of AL (A, B, and C): According to the grading system suggested by Rahbari et al in the aforementioned study,^[14]^ AL is classified into^[3]^ stages depending on the necessity of therapeutic or surgical intervention.Grade A: no active therapeutic intervention requiredGrade B: requires active therapeutic intervention, but manageable without relaparotomyGrade C: requires relaparotomy2.Operating time (time frame: 1 day): The duration of surgical procedure in minutes.3.Circular stapler dysfunction rate (time frame: 1 day): The rate of circular stapler inability to create a colorectal anastomosis in a way declared by the manufacturer.4.Anastomotic bleeding rate (time frame: 30 days): The rate of bleeding from the line of stapled anastomosis verified by proctoscopy.5.Reintervention rate (time frame: 6 weeks): The rate of repeat surgeries due to anastomotic leakage.6.Early postoperative complications rate (time frame: 30 days): The rate of complications in 1st 30 days after surgery, Clavien–Dindo postoperative complication grades I to V.7.The postoperative hospital stay (time frame: 1 month): The number of days from the 1st day after operation to discharge.8.Complications of defunctioning stoma (time frame: 3 months): The rate of complications related to defunctioning stoma.9.Overall quality of life (time frame: 7 days before surgery, and 1, 3, 6, and 12 months after surgery): Assessed with patient-reported questionnaire SF-36. A total score in each of 8 sections will be calculated and transformed into a 0 to 100 scale with a score of 0 equivalent to maximum disability and a score of 100 equivalent to no disability.10.Cancer-related quality of life (time frame: 7 days before surgery, and 1, 3, 6, and 12 months after surgery): Assessed with patient-reported questionnaire European Organization for Research and Treatment of Cancer (EORTC) QLQ-C30 with supplementary module EORTC QLQ-CR29. A total score in each of 4 modules (functional scale, global health status, symptom scale, colorectal cancer module) will be calculated and converted into a 0 to 100 scale. For functional scale, global health status scale, and colorectal cancer module a score of 0 is equivalent to maximum disability and a score of 100 is equivalent to no disability. For symptom scale a score of 100 is equivalent to maximum disability and a score of 0 is equivalent to no disability.11.Manifestation of LARS (time frame: 7 days before surgery, and 1, 3, 6, and 12 months after surgery): Assessed with patient-reported questionnaire LARS, total score will be calculated (minimum 0, maximum 42) for each patient and also each patient will be assigned to either “no LARS” group (total score 0–20), “minor LARS” group (total score 21–29), or “major LARS” group (total score 30–42).12.Manifestation of fecal incontinence (time frame: 7 days before surgery, and 1, 3, 6, and 12 months after surgery): Assessed with patient-reported questionnaire CCIS, total score will be calculated (minimum 0, maximum 20) for each patient, where 0 means perfect continence and 20, complete incontinence.13.Adverse events rate (time frame: 12 months): The rate of adverse events related to circular stapler usage.14.Serious adverse events rate (time frame: 12 months): The rate of serious adverse events related to circular stapler usage.

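### Stoma complications are counted only to 3 months although a leak may delay reversal, and no outcome grades complications of the closure operation

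*Protocol article*

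**What the plan says.** Under both surgical approaches (Sections 2.3.3.1 and 2.3.3.2) a preventive transverse colostomy is made, so closure is a second planned operation. Section 2.3.5 gives its timing: "At weeks 4 to 6, according to the standard protocol, the preventive stoma is closed". Section 2.4.1 adds that the time between the resection and reversal "may differ significantly between subjects due to variability of AL presentation and symptoms". It gives no latest date. The abstract states 12 months of monitoring after the resection.

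Five items of Section 2.4.2 bear on stoma and closure complications:

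- Item 8: "Complications of defunctioning stoma (time frame: 3 months): The rate of complications related to defunctioning stoma". The start of the clock is not stated.
- Item 6, graded by Clavien–Dindo: "Early postoperative complications rate (time frame: 30 days): The rate of complications in 1st 30 days after surgery". Section 2.3.4 also ends the early postoperative period 30 days after surgery.
- Item 5: "Reintervention rate (time frame: 6 weeks): The rate of repeat surgeries due to anastomotic leakage".
- Item 13: "Adverse events rate (time frame: 12 months): The rate of adverse events related to circular stapler usage".
- Item 14: "Serious adverse events rate (time frame: 12 months): The rate of serious adverse events related to circular stapler usage".

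**The concern.** The protocol itself ties the duration of the stoma to the leak, which is the primary outcome. A stoma that is still open at 3 months stays at risk of complications and still has a closure operation ahead of it, but item 8 has stopped counting by then. The primary outcome window, by contrast, runs to reversal whenever that occurs. A patient can thus still be under observation for the primary endpoint after stoma complications have ceased to be recorded as an outcome. If one stapler leaks more, more of its patients may be in this position, and the 3-month figure would understate that arm's full stoma burden by more.

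Separately, the closure operation is planned for every patient but falls almost entirely after the only graded complication window has ended. A reader of the results could not tell how severe its complications were in either arm.

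**Working it through.** The plan gives no computed figure on this point, so the check sets the stated windows against each other. Day 0 is the resection. That item 8 starts there, and that 3 months is 90 days, are assumptions.

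**1. Graded window (item 6) against planned closure.** Weeks 4 to 6 are days 28 to 42.

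- Closure on day 28: 30 − 28 = 2 days of graded follow-up.
- Closure on day 42: 30 − 42 = −12, so the window ended 12 days earlier.
- If closures are spread evenly over days 28 to 42 (assumption), (30 − 28)/(42 − 28) = 2/14 = 14% occur by day 30. Counting whole days, it is 3/15 = 20%.
- Average graded follow-up after closure under the same assumption: (2 × 2/2)/14 = 0.14 days, which is 0.14/30 = 0.5% of the first 30 days.

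No on-schedule closure has 30 days of graded follow-up.

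**2. Stoma window (item 8) against planned closure.**

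- Closure on day 42: 90 − 42 = 48 days remain.
- Closure on day 28: 90 − 28 = 62 days remain.
- Latest closure with a full 30 days inside the window: 90 − 30 = day 60.

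For a patient closed on schedule, item 8 spans the whole stoma period and roughly 7 to 9 weeks after it. Closures between days 60 and 90 lose part of their first 30 days. Stomas open beyond day 90 lose their later complications and the whole closure.

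**3. Whether another item fills the gap.**

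| Item | Ends | Restricted to | Covers closure complications? |
|---|---|---|---|
| 5 | 6 weeks | repeat surgery for a leak | No |
| 6 | 30 days | none | Almost none |
| 8 | 3 months | stoma-related | Possibly, ungraded; not stated |
| 13, 14 | 12 months | stapler-related events | Only if attributed to the stapler |

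**4. How many patients could be affected.** Inputs from Section 2.6: 77 per arm, an 18% leak rate at the centre, and a 30% leak rate expected for the 3-row device. That section also describes a 12-point advantage for the 3-row device, which contradicts these rates. That is a separate matter, and the two rates serve here only as a lower and a higher value. The share f of leaking patients whose stoma stays beyond 3 months is not in the document, so it is varied. Patients at risk = 77 × leak rate × f.

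| f (assumed) | 18% leak rate | 30% leak rate | Difference |
|---|---|---|---|
| 10% | 77 × 0.18 × 0.10 = 1.4 | 77 × 0.30 × 0.10 = 2.3 | 0.9 |
| 50% | 77 × 0.18 × 0.50 = 6.9 | 77 × 0.30 × 0.50 = 11.6 | 4.6 |
| 100% (limit) | 13.9 | 23.1 | 9.2 |

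These are patients still at risk when counting stops. Only those with a first stoma complication after that date would change the reported proportion, so missed events are fewer.

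**The case against.** A fixed window applied identically to both arms is a fair comparison of the risk within that window. Three months is more than twice the latest planned closure time of 42 days. Item 6 is labelled as an early outcome and matches the protocol's own definition of the early period, so it is not wrong as written; grading a later operation would be an addition. Leak harm also appears elsewhere: the primary outcome, leak severity grades A to C, leak reintervention, quality of life to 12 months, and stapler-related events to 12 months. Section 2.9.4 also requires all adverse events to be reported, and the schedule in Figure 2 is not available here. Stoma complications are not named among the objectives in Section 1.2.

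Most of this stands and limits the point. It rules out two stronger readings. A reader might infer that most of the second operation goes uncounted. The documents do not support that: an on-schedule closure lies inside item 8's window with 48 to 62 days to spare, and what is missing is grading and a statement that its complications count. A reader might also infer that the between-arm comparison is biased. It is not: it estimates a 3-month risk validly, but a narrower quantity than the stoma burden over the trial's follow-up.

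What remains is that no listed outcome counts stoma complications after 3 months, although the protocol expects reversal to vary with the leak. Reporting events to the ethics committee and sponsor is not the same as an outcome compared by arm.

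**Conclusion.** The point holds as a limited gap in a secondary safety outcome. Complications of stomas kept beyond 3 months, or around such late closures, are not counted, and the loss can fall more on the arm with more leaks. Its size is unknown because the document gives no stoma duration after a leak. Under the assumed 10% to 50% delay, the difference between an arm at 18% and one at 30% is about 1 to 5 patients at risk. No outcome grades the closure operation, and item 8 leaves open whether its complications count; this second part rests on the stated dates alone and needs no assumption about delay.

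The documents do not show that a leak reaches patients mainly as a prolonged or permanent stoma, and the point does not depend on that. The noninferiority conclusion, the primary analysis and the sample size are unaffected.

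**What to change.** In item 8, count stoma complications over a fixed 12 months from the resection in both arms, and state that start date. Keep the 3-month figure alongside if wanted; it fits the interim analysis, which is timed after 3 months of follow-up. State that complications of the closure operation are included and graded by Clavien–Dindo. Report stoma status at 12 months by randomised arm as a descriptive item.

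A fixed 12 months is preferable to counting until some days after closure, because observation time would then depend on a post-randomisation event linked to the leak. One small limit remains: a closure in the last 30 days of follow-up would have an incomplete post-closure period.

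The cost is some extra eCRF coding: grading of closure complications and stoma status at 12 months. The closure date is already needed because reversal ends the primary outcome window. The existing 12-month follow-up suffices, so no visits are added, and the sample size does not change.

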#### Data monitoring

2.9.4

There is no data monitoring committee designated to this trial. Any adverse and serious adverse events will be immediately reported to the principal investigator and the primary sponsor. An interim analysis will be performed after 20 patients in each study group will have completed 3-month follow-up. All AEs and SAEs will be immediately reported to the local ethics committee, study director, and the sponsors.

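### The only 12-month AE and SAE outcomes count events judged stapler-related; no all-cause AE or SAE rate is compared by arm after day 30

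*Protocol article*

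**What the plan says.** Protocol article, Secondary outcome measures (2.4.2):

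- Item 13, with a 12-month time frame: "The rate of adverse events related to circular stapler usage".
- Item 14: "Serious adverse events rate (time frame: 12 months): The rate of serious adverse events related to circular stapler usage".
- Item 6, limited to 30 days: "The rate of complications in 1st 30 days after surgery, Clavien–Dindo postoperative complication grades I to V". It carries no relatedness filter.
- Item 8: "Complications of defunctioning stoma (time frame: 3 months): The rate of complications related to defunctioning stoma".
- Item 5 counts repeat surgery for leakage only, to 6 weeks.

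Primary outcome measure (2.4.1): leakage documented by imaging, from surgery until stoma reversal, usually at 4 to 6 weeks.

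Statistical methods (2.9.3): overall survival is compared between arms by the log-rank test.

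Trial design (1.3) and Blinding (2.8.2): patient and outcomes assessor are blinded. The eCRF leaves out the stapler used but takes in the operation note.

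Data monitoring (2.9.4): "Any adverse and serious adverse events will be immediately reported to the principal investigator and the primary sponsor". No relatedness filter applies to this reporting. There is no data monitoring committee.

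**The concern.** Assessing the safety of a new device is a stated aim of the trial (Background and rationale; Discussion in the abstract). An outcome that counts only device-related events passes every event through a judgement about cause before it enters the comparison. If that judgement leans differently in the two arms, the comparison shifts although the true event rates are equal. A real excess can be hidden in the same way.

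The setting makes a lean plausible. The comparator has been in conventional use for over 10 years, the other device is new, and the surgeon who fires the stapler knows which one it is. Before day 30 the Clavien–Dindo rate gives a check that needs no attribution. After day 30 no general rate does. Stoma reversal, scheduled at weeks 4 to 6, falls mostly after that point. Background and rationale also names anastomotic stricture as a possible complication. It is not a listed outcome, so a stricture found after day 30 enters a listed complication rate only if it is judged stapler-related.

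**Working it through.** **Step 1. Which outcomes cover the time after day 30, and do they need stapler attribution?**

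| Outcome | Runs to | Stapler attribution needed? | General event rate? |
|---|---|---|---|
| Clavien–Dindo complications (item 6) | day 30 | no | yes |
| Leakage (primary) | stoma reversal, usually 4–6 weeks | no | no, leakage only |
| Reintervention (item 5) | 6 weeks | no, but tied to leakage | no |
| Stoma complications (item 8) | 3 months | no | no, stoma only |
| SF-36, QLQ-C30, LARS, CCIS (items 9–12) | 12 months | no, reported by blinded patients | no, not event rates |
| Overall survival | not stated in 2.9.3 | no | death only |
| AE and SAE rates (items 13, 14) | 12 months | **yes** | only after the filter |

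No row gives a general AE or SAE rate, free of attribution, beyond day 30. Day 30 is 30/365 = 8.2% of the follow-up year. That is a share of calendar time, not of events, since early postoperative events are probably over-represented in it.

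**Step 2. Can the judgement of relatedness be influenced by knowing the device?**

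The surgeon knows the device. The outcomes assessor is declared blinded and the eCRF omits the stapler, but the operation note in the eCRF may identify it unless redacted. The article does not tie the judgement of relatedness to the blinded assessor. So the text neither states unblinded attribution nor rules it out.

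**Step 3. How large could the effect be?**

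The documents give no AE or SAE rates and no attribution shares, so every rate and share below is an assumption. Only n = 77 per arm comes from Sample size (2.6). The plan states no figure on this point that could be reproduced.

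With the same true risk p in both arms and shares a0 and a1 judged related, the apparent difference is p × (a1 − a0).

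- p = 20%, gap 10 points: 0.20 × 0.10 = 0.02, or 2 points (77 × 0.02 ≈ 1.5 patients).
- p = 20%, gap 30 points: 0.20 × 0.30 = 0.06, or 6 points (77 × 0.06 ≈ 4.6 patients).

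The chance of a significant result in the direction of the bias (two-sided 0.05) is Φ[(d − 1.96·SE0)/SE1]. Here d is the absolute apparent difference, SE0 the pooled and SE1 the unpooled standard error. Without bias this one-directional chance would be 2.5%.

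| True risk, both arms | Related: 50% vs 40% | Related: 50% vs 30% |
|---|---|---|
| 20% | 10% vs 8%: 6% | 10% vs 6%: 15% |
| 40% | 20% vs 16%: 9% | 20% vs 12%: 27% |
| 60% | 30% vs 24%: 13% | 30% vs 18%: 41% |

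**Step 4. What does even-handed filtering cost?**

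Take a true all-cause excess of 40% versus 60%.

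- All events counted: power about 70%.
- Half judged related in both arms (20% vs 30%): about 30%.
- 30% judged related in both arms (12% vs 18%): about 18%.

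This assumes that the excess is spread over all events in proportion. If the device affected only events that are correctly judged related, the filter would lose nothing and would remove noise.

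**The case against.** **Other comparisons after day 30.** A reader might infer that the whole safety comparison after day 30 rests on attribution. It does not. Imaging-documented leakage, stoma complications, survival and the blinded patients' questionnaires need no stapler attribution. What stands is narrower: each is cause-specific, limited to death, or not an event rate.

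**Blinding.** A reader might also infer that treating staff who know the device will decide relatedness. The article does not say so. Only the surgeon's knowledge is certain, and the blinded assessor and the eCRF omission are real safeguards. This objection stands: biased attribution is a possibility.

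**Detail left to a fuller document.** Who judges relatedness, and which AE tables are produced, commonly sit in the full protocol or analysis plan, which are not shown. That silence alone is no finding. But the filter is part of the stated outcome definition, so the point rests on what the article fixes.

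**Fit with the objectives.** The key secondary safety objective concerns anastomosis-related complications, and a device-related rate suits it. All-cause counts add unrelated events and noise. This too stands, and it is why the related rates should be kept and not replaced or demoted.

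**Magnitude.** At an assumed 20% risk, a 10-point attribution gap moves about 1.5 patients of 77, which is small.

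**Conclusion.** The concern holds in a limited form. The only AE and SAE outcomes to 12 months are restricted to stapler-related events, and the only unfiltered general complication rate ends at day 30. For the remaining eleven months no planned all-cause AE or SAE rate by arm can show whether attribution has shaped the comparison.

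The size of any bias is unknown. The 2 to 6 points rest on an assumed equal true SAE risk of 20% and an assumed attribution gap of 10 to 30 points, and could go in either direction. The documents do not support a claim that bias will occur. The leakage outcome and the primary non-inferiority question are not affected.

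**What to change.** In Secondary outcome measures, add to items 13 and 14 the rates of all AEs and all SAEs to 12 months regardless of attribution, reported and compared by arm. Keep the stapler-related rates beside them. State that relatedness is judged by someone blind to the device, with device-identifying text in the operation note masked for that person.

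The cost is wording in two outcomes and one extra table. Data monitoring (2.9.4) already requires all AEs and SAEs to be reported, so no new data are needed. Masking the note adds a small administrative step. The downside is that all-cause rates include events unrelated to the device and are noisier for device-specific effects; showing both rates deals with that.
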